**Fig. 2 Fig2:**
[figure not shown]
Application of SAEM-SC. LF-rTMS over the M1 region hot spot (motor cortex at the left hemisphere) and SA stimulation of MS6 and MS7 at the upper limb regions of the right hemisphere

The SA therapy will be conducted by a doctor who is experienced in Korean medicine, is affiliated with Dong-Shin Traditional Korean Medicine University Hospital, and has more than 2 years of clinical experience. rTMS will be conducted by a doctor affiliated with the Department of Physical and Rehabilitation Medicine at Chonnam National University Hospital.

During the clinical trial period, all participants are allowed routine management, existing medications (medications for hypertension, diabetes, hyperlipidemia, and improvement of brain function), and medications to maintain and improve health status. However, patients are not allowed to engage in treatments to improve CI other than the therapies used in this study.

All medical devices will be inspected by coordinators who will manage scalp acupuncture needles ([name], Resident of Department of Korean Medicine Rehabilitation, College of Traditional Korean Medicine, Dong-Shin University) and rTMS ([name], occupational therapist, Department of Physical and Rehabilitation Medicine at Chonnam National University Hospital). Coordinators will record the results of the check-ups in the management register.

### Outcome measurements

Primary and secondary outcome assessments will be conducted at baseline (before intervention), 3 weeks after the first intervention, and 4 weeks after completion of intervention.

### Primary outcome

Since the objective of this study is to investigate the efficacy of SAEM-CS on motor function recovery in patients with cerebral infarction, the primary outcome will be assessed via changes on the Fugl‐Meyer Assessment (FMA) scale for motor function. The FMA is widely used as a qualitative measure of motor function and is used in the current study to assess upper and lower limb function. The FMA is categorized into 50 items based on a six-stage recovery process of Brunnstrom’s hemiplegia classification and progress record. This assessment is an ordinal scale, in which 0 is given for unable to perform, 1 for partial performance, and 2 for complete performance. The FMA has a possible total score of 100, 66 points of which apply to the upper limbs and 34 points to the lower limbs [16].

### Secondary outcomes

Secondary outcome measures will be assessed changes in the National Institutes of Health Stroke Scale (NIHSS) score, Modified Barthel Index (MBI), Functional Independence Measurement (FIM) score, Korean Mini-Mental State Examination (K-MMSE) score, American Speech-Language-Hearing Association National Outcomes Measurement System (ASHA-NOMS) Swallowing Scale score, Functional Ambulation Categories (FAC), European Quality of Life-5 Dimensions (EQ-5D), Modified Ashworth Scale (MAS) score, Hand Grip Strength Test, MEPs, mRS score, and 9-Hole Peg Test (9HPT).

The NIHSS is a scale that was developed by the United States National Institutes of Health, and provides useful information on the severity, prognosis, and early treatment of stroke [9].

The MBI is an assessment tool used to objectively evaluate performance of everyday movements on 10 items: personal hygiene, bathing, eating, toilet use, ability to climb stairs, ability to dress, bowel/bladder function, walking function, capability of getting into and out of a chair/bed, and mobility [21].

The FIM is an assessment of everyday movement performance that evaluates 13 detailed items of motor FIM and 5 detailed items of cognitive FIM. The FIM has a total possible score of 18–126, and each item is divided into seven stages, allowing for a comparably detailed assessment. Higher FIM scores indicate higher functional independence [22].

The MMSE is a brief global instrument used to assess cognitive abilities and has been translated into Korean (K-MMSE) [23]. The K-MMSE is a quick screening assessment tool that was developed to evaluate cognitive function and dementia in elderly patients with suspected dementia or patients with brain damage. The instrument consists of measures used to assess orientation, recall, attention and calculation, language, judgment, and understanding. A score ≥24 points indicates definitive normal, 20–23 indicates suspected dementia, and ≤19 indicates definitive dementia [24].

The ASHA-NOMS is a seven-stage dysphagia scale developed by the American Speech-Language-Hearing Association to evaluate severity of dysphagia for items such as parenteral hyperalimentation, whether independent eating is possible, use of compensative skills for eating, and diet limitations [25].

The FAC is designed to evaluate walking ability where a patient’s independent walking ability is categorized into six ranks: 0 = unable to walk, 1 = direct assistance required by the therapist, 2 = intermittent and direct assistance required by the therapist, 3 = able to walk independently but requires observation, 4 = able to walk independently but requires assistance on uneven surfaces, and 5 = able to independently walk on even surfaces [26].

The EQ-5D evaluates quality of life in five fields including exercise ability, self-management, daily activities, pain/discomfort, and anxiety/depression. Each field is divided into three levels with 1 indicating a good state of health. The EQ-5D also includes a visual analog scale in which a subject indicates subjective and overall individual health status on a vertical scale where the best health state is 100 points and the poorest health state is 0 points [27].

The MAS assesses muscles by measuring spasticity in the wrist and elbow joints while the joints are maximally bent. Scores range from 0, where there is no increase in muscle tone, to 4, where there is contracture in bent and straight muscles and/or joints [15].

The Hand Grip Strength Test evaluates muscle strength in the hands and is conducted twice in six stages; the higher value (kg) of the two tests is recorded [9].

In the current study, MEPs are evoked by stimulating the primary motor cortex on representation of hand grip muscles without pain, and responses of the FDI muscle are then observed. MEPs are useful to predict functional recovery in CI. Here, the cerebral hemisphere is magnetically stimulated in a figure 8 shape while the patient is lying down. Stimulations increase in intensity from 0 to 100 % until the MEP with the shortest latency occurs. The latency and the amplitude of the MEP responses are recorded [28].

The mRS is a six-point, ordinal hierarchical scale that describes “global disability” with a focus on mobility. The mRS is often used in contemporary stroke studies as a measure of premorbid ability and is used to assist in the selection of patients and as a final outcome measure. The mRS uses a 5-min non-standardized interview, and has six potential scores (0–5), which describe a full range of stroke outcomes; a score of 6 denotes death [29, 30].

The 9HPT is useful in measuring dexterity in relatively well-recovered patients. In the current study, participants are instructed to place nine pegs into nine holes on a board as fast as possible. Scores are computed as pegs/s, averaged over three trials, and normalized to the average score of the unaffected hand (range 0–1; 0 = cannot do) [31].

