**Methods/design:**

This study is a prospective, outcome assessor-blinded, randomized controlled clinical trial with a 1:1:1:1 allocation ratio. Participants with motion or sensory disabilities caused by a first-time cerebral infarction (*n* = 60) that had occurred within 1 month of the study onset will be randomly assigned to control, SA, rTMS, or SAEM-CS groups. All groups will receive two sessions of conventional rehabilitation treatment per day. The SA group will receive SA on the upper limb area of MS6 and MS7 (at the lesional hemisphere) for 20 min, the rTMS group will receive low-frequency rTMS (LF-rTMS) treatment on the hot spot of the M1 region (motor cortex at the contralesional hemisphere) for 20 min, and the SAEM-CS group will receive LF-rTMS over the contralesional M1 region hot spot while receiving simultaneous SA stimulation on the lesional upper limb area of MS6 and MS7 for 20 min. SA, rTMS, and SAEM-CS treatments will be conducted once/day, 5 days/week (excluding Saturdays and Sundays) for 3 weeks, for a total of 15 sessions. The primary outcome will be evaluated using the Fugl‐Meyer Assessment, while other scales assessing cognitive function, activities of daily living, walking, quality of life, and stroke severity are considered secondary outcome measures. Outcome measurements will be conducted at baseline (before intervention), 3 weeks after the first intervention (end of intervention), and 4 weeks after intervention completion.

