## Background

Cerebral infarction (CI) is one of the most commonly reported cerebral vascular diseases, accounting for about 70 % of strokes [1]. The incidence, mortality, and recurrence rates of CI are high, and CI usually leads to serious damage of the central nervous system [2]. Despite a considerable amount of research on effective treatments for stroke, there is still no single intervention that clearly and definitively contributes to stroke recovery. Therefore, stroke treatment strategies should combine multiple disciplines, such as neurology, rehabilitation medicine, and traditional medicine [3]. Scalp acupuncture (SA) is one of several specialized acupuncture techniques, and it involves a filiform needle being used to penetrate specific stimulation areas on the scalp [4]. SA therapy for ischemic and hemorrhagic stroke has been empirically established and is used worldwide [5–8]. The local application of repetitive transcranial magnetic stimulation (rTMS) influences the neural excitability of selected brain areas [9], and it has been reported that low-frequency stimulation (1 Hz) suppresses local neural activities [10, 11], whereas high-frequency stimulation (≥5 Hz) activates local neural activities [12]. Both high-frequency rTMS (HF-rTMS) applied to the lesional hemisphere and low-frequency rTMS (LF-rTMS) applied to the contralesional hemisphere are beneficial for upper limb hemiparesis in patients with chronic stroke [11, 13–17] and in the early phase of stroke [9, 18–20].

Conventional medical physicians and doctors who practice traditional Korean medicine (TKM) tend to focus on each field’s treatment methods in separate medical systems. Unfortunately, efforts to improve the treatment rates of incurable diseases through collaborative research and via the fusion of treatment techniques are lacking. The purpose of this study is to explore the efficacy and safety of SA and electromagnetic convergence stimulation (SAEM-CS), which was developed through a collaborative study between the Department of Physical and Rehabilitation Medicine at Chonnam National University Hospital and the Departments of Acupuncture and Moxibustion Medicine and Traditional Korean Medicine Rehabilitation at Dong-Shin University. Thereafter, we will compare SAEM-CS to conventional stroke rehabilitation, SA, and rTMS therapeutic approaches.

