5. Practitioner background	5) Description of participating acupuncturists	Korean medicine doctor with the following qualifications: 6 years of formal university training in Korean medicine, a license, and at least 2 years of clinical experience
6. Control or comparator interventions	6a) Rationale for the control or comparator in the context of the research question, with sources that justify the choice	Wang Y, Shen J, Wang XM, Fu DL, Chen CY, Lu LY, et al. Scalp acupuncture for acute ischemic stroke: a meta-analysis of randomized controlled trials. *Evid Based Complement Altern Med* 2012;2012:480950; Lee SJ, Shin BC, Lee MS, Han CH, Kim JI. Scalp acupuncture for stroke recovery: a systematic review and meta-analysis of randomized controlled trials. *European J Integr Med*. 2013;5:87–99
	6b) Precise description of the control or comparator; details for items 1–3 above with the use of sham acupuncture or any other type of acupuncture-like control	Conventional stroke rehabilitation therapy for control, rTMS, and SAEM-CS groups. LF-rTMS applied to the hot spot of the M1 region (the motor cortex at the contralesional hemisphere) for the rTMS group and LF-rTMS applied to the same M1 and simultaneous SA stimulation over the upper MS6 and MS7 regions of the lesional hemisphere for the SAEM-CS group

The rTMS method will be conducted as follows: a 70-mm figure 8 coil and a Magstim Rapid stimulator (Magstim Co., Dyfed, UK) is used to deliver 1 Hz of rTMS to the skull of the contralesional hemisphere at the site that elicits the largest motor evoked potentials (MEPs) in the first dorsal interosseous (FDI) muscle of the unaffected upper limb. One LF-rTMS session consists of 1200 pulses and lasts for 20 min. The stimulation intensity is set to 80 % of the motor threshold of the FDI muscle, which is defined as the lowest intensity of stimulation that provokes MEPs [15, 16]. All patients sit in a reclining wheelchair and are asked to relax as much as possible, with their heads strapped to a headrest [9].

The SAEM-CS treatment method will be conducted as follows: the above-described SA and LF-rTMS therapies are performed simultaneously. After SA treatment of MS6 and MS7 on the lesion side, LF-rTMS stimulation is conducted on the contralateral hemisphere of the opposite side of the lesion for 20 min (Fig. 2).

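### The 9-Hole Peg Test score is divided by the unaffected hand, the hand whose motor hot spot is stimulated in two of the four arms; unless that denominator is fixed at baseline, treatment can distort some contrasts

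*Protocol article*

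**What the plan says.** The protocol article, under Secondary outcomes, gives the 9HPT scoring rule: pegs per second, as the mean of three trials, "normalized to the average score of the unaffected hand", with a range from 0 (cannot do) to 1. The score is therefore a ratio of affected-hand to unaffected-hand speed.

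Under Intervention, the rTMS method is to "deliver 1 Hz of rTMS to the skull of the contralesional hemisphere", and the coil is placed "at the site that elicits the largest motor evoked potentials (MEPs) in the first dorsal interosseous (FDI) muscle of the unaffected upper limb". The stimulated site is thus located from a hand muscle of the limb that supplies the 9HPT denominator. On dose, "One LF-rTMS session consists of 1200 pulses and lasts for 20 min", with 15 sessions over 3 weeks.

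Two arms receive this stimulation. One is the rTMS arm. For the other, the Abstract says "the SAEM-CS group will receive LF-rTMS over the contralesional M1 region hot spot while receiving simultaneous SA stimulation". The control and SA arms receive no rTMS. The Background states that "low-frequency stimulation (1 Hz) suppresses local neural activities".

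Under Outcome measurements, primary and secondary outcomes are assessed at baseline, at 3 weeks, and 4 weeks after the intervention ends. Under Data analysis, the 9HPT is one of the outcomes compared by repeated measures ANOVA, with Tukey's test between groups. Nothing says whether the unaffected hand is timed again at each visit or only at baseline.

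**The concern.** A normalising quantity is safe in a randomised comparison when treatment cannot change it, for example because it was measured before treatment. Here the denominator is the performance of a hand whose cortical representation is the direct target of stimulation in half of the patients (30 of 60). If it is measured after treatment, it becomes a post-randomisation quantity that treatment can alter in two arms and not in the other two.

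The ratio cannot separate the two ways in which it may rise: the affected hand getting faster, or the unaffected hand getting slower. A decline in the good hand would then be scored as benefit. The unaffected hand's speed is not listed as an outcome of its own, so the ratio alone would not show this. The exposed contrasts include SAEM-CS versus conventional therapy and SAEM-CS versus SA, both named in the Objective section.

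**Working it through.** The article states no numerical figure for the 9HPT, so there is none to reproduce. The check has four parts.

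**1. Which arms are exposed.** 1200 pulses at 1 Hz take 1200 / 60 = 20 min, which agrees with the stated session length. Over 15 sessions this is 15 × 1200 = 18,000 pulses aimed at the unaffected hand's hot spot, in the rTMS and SAEM-CS arms (15 + 15 = 30 patients). The control and SA arms (30 patients) receive none.

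**2. Sensitivity of the ratio.** Let A be affected-hand speed, U unaffected-hand speed, and R = A / U. If A is unchanged and U changes by a fraction d, then R′ = A / [U(1 + d)] = R / (1 + d). The relative change is 1/(1 + d) − 1. The values of d and the starting ratio R = 0.50 are assumptions; the article gives neither.

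| d (change in unaffected hand) | R′ | Relative change in ratio |
|---|---|---|
| −10% | 0.556 | +11.1% |
| −5% | 0.526 | +5.3% |
| −2% | 0.510 | +2.0% |
| 0 | 0.500 | 0 |
| +2% | 0.490 | −2.0% |
| +5% | 0.476 | −4.8% |
| +10% | 0.455 | −9.1% |

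The relative change does not depend on R. A patient scored 0 (cannot do the test) stays at 0, because 0 / (1 + d) = 0.

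**3. Which contrasts move.**
- rTMS or SAEM-CS versus control or SA: one side is multiplied by 1/(1 + d) and the other is not, so a spurious difference arises with no true effect on the affected hand.
- rTMS versus SAEM-CS: if stimulation acts alike in both arms, both sides are multiplied by the same factor. A true difference D becomes D / (1 + d), and a zero difference stays zero.
- SA versus control: neither side is altered.
- Denominator fixed at baseline, or raw affected-hand pegs per second: d does not enter the score, so the distortion is 0 for any d.

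**4. What this could do to the test.** A null simulation used 15 patients per arm and 4000 runs per setting. It assumed a mean baseline ratio of 0.50 (SD 0.15), the same mean gain of 0.10 in every arm, and the denominator changed by d in the two rTMS-containing arms. The test was a one-way ANOVA on change in ratio at the 0.05 level. This simplifies the planned three-visit repeated measures ANOVA, and all of these inputs are assumed except the arm size and the 0.05 level.

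| d | SD of change 0.10 | SD 0.15 | SD 0.20 |
|---|---|---|---|
| 0 | 0.047 | 0.049 | 0.044 |
| −2% | 0.070 | 0.055 | 0.053 |
| −5% | 0.136 | 0.083 | 0.073 |
| −10% | 0.482 | 0.240 | 0.145 |
| +5% | 0.137 | 0.083 | 0.068 |
| +10% | 0.389 | 0.187 | 0.126 |

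Entries are false-positive rates. A change of 2% does little. A change of 5% matters if the outcome is not very variable, and a change of 10% matters throughout the range.

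**The case against.** The strongest reply is that nothing in the article shows the denominator moving. The Background speaks of suppressed neural activity and not of slower peg placement. Stimulation is set at 80% of motor threshold. No statement says that an effect on the unaffected hand would last to the end-of-treatment visit, still less to the visit 4 weeks later. That stands: a reader might infer that treatment does slow the unaffected hand and that the bias must favour the rTMS-containing arms, but the article supports neither step. It fixes no sign, and if the unaffected hand became faster the ratio would fall. Nor would slowing favour every arm under test, since SA is also an experimental arm and would be put at a disadvantage.

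A second reply is that the denominator may already be the baseline value, in which case there is no distortion. This also stands as a possibility. Re-measurement is the more natural reading, because the score is defined without reference to baseline and the outcomes are assessed at three visits, but the text does not settle it.

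A third reply is that a same-visit denominator has a purpose: it can absorb practice effects between visits, and the rule is taken from a cited source. Practice effects should, however, be similar across randomised arms, so losing that correction costs the between-arm comparison little.

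Finally, the 9HPT is one of 12 secondary outcomes in an exploratory pilot. That limits the consequence but does not remove the problem.

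**Conclusion.** The point holds in conditional form. The scoring rule and the intervention, both stated in the article, leave the 9HPT open to treatment-dependent distortion if the unaffected hand is re-measured after treatment. The contrasts at risk are rTMS or SAEM-CS against control or SA. The rTMS versus SAEM-CS contrast is largely spared, provided that the stimulation affects the unaffected hand alike in both arms.

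The size is unknown. Assumed slowing of 2%, 5% or 10% would raise the ratio by 2.0%, 5.3% or 11.1% with no gain in the affected hand, and speeding would lower it. The false-positive rates above rest on further assumed inputs and only illustrate the range.

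The Fugl-Meyer primary outcome is not normalised to the other limb, so neither the primary analysis nor the sample size is affected. The change is still worth making, because it removes the distortion whatever its size or direction.

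**What to change.** In the 9HPT paragraph under Secondary outcomes, state when the denominator is measured, and adopt one of two rules:

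- divide the affected-hand score at every visit by the unaffected hand's baseline (pre-treatment) score; or
- analyse affected-hand pegs per second (mean of three trials, with cannot do scored as 0) without normalisation.

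In either case, where the unaffected hand is measured after baseline, report its pegs per second by arm and visit, so that any change in that hand is visible in its own right.

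The cost is a sentence or two of wording. It needs no change to treatment and no added assessment: baseline timing of the unaffected hand is already needed for the baseline score, and the separate report is asked for only where later timings exist. The one small loss is that a baseline denominator no longer absorbs practice effects between visits.

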### Incidence of adverse events

Adverse events refer to undesirable and unintentional signs, symptoms, or diseases that appear after treatment in a clinical trial. Importantly, these events may not have a causal relationship with the therapy employed; nevertheless, they should be documented. Adverse events expected from this study include nausea, vomiting, headaches, dizziness, skin irritation, convulsions, and objective worsening of existing symptoms. The CRC will record adverse events, their progress, and their causal relationship with treatments in detail and will report them to the principal investigator (PI) and Institutional Review Board (IRB). If serious adverse events occur, defined as those causing severe disability or malfunction, then appropriate measures will be taken and incidents will be immediately reported to the PI and IRB.

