### Data monitoring

The Data Monitoring Committee (DMC) is composed of the PI and coordinators who are in charge of scalp acupuncture needles ([name], resident of the Department of Korean Medicine Rehabilitation, College of Traditional Korean Medicine, Dong-Shin University) and rTMS ([name], an occupational therapist in the Department of Physical and Rehabilitation Medicine at Chonnam National University Hospital). If needed, they will report the monitoring results to the PI. Finally, this study is independent from any sponsors.

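### The serious adverse event definition covers only severe disability or malfunction, so read literally the immediate-reporting rule misses deaths, life-threatening events, hospitalisations and convulsions with recovery

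*Protocol article*

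**What the plan says.** Incidence of adverse events sets up two reporting streams.

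- **All adverse events.** These are documented whether or not treatment caused them. The clinical research coordinator (CRC) is responsible: "The CRC will record adverse events, their progress, and their causal relationship with treatments in detail". The CRC also "will report them to the principal investigator (PI) and Institutional Review Board (IRB"). No time limit is given.
- **Serious adverse events.** The definition reads: "If serious adverse events occur, defined as those causing severe disability or malfunction, then appropriate measures will be taken". For this class alone the section sets an urgent reporting duty: "incidents will be immediately reported to the PI and IRB".

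The section also lists what is foreseen: "Adverse events expected from this study include nausea, vomiting, headaches, dizziness, skin irritation, convulsions, and objective worsening of existing symptoms". No event on that list has a seriousness rule of its own.

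On oversight, Data monitoring says: "The Data Monitoring Committee (DMC) is composed of the PI and coordinators who are in charge of scalp acupuncture needles", together with the coordinator for the rTMS device. On reporting it says: "If needed, they will report the monitoring results to the PI". The Intervention section gives these coordinators an operational role: "All medical devices will be inspected by coordinators who will manage scalp acupuncture needles", and likewise for rTMS.

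**The concern.** The seriousness definition decides which events are reported at once. Here it is stated outright, so this is not a detail that the article simply leaves to a fuller document. It names two consequences, severe disability and malfunction, and omits the other usual criteria.

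Three features of this trial make the gap matter.

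- The abstract, the Background and Study design all name safety, next to efficacy, as something the study investigates. The treatment is described there as newly developed.
- The authors recognise the hazard. Convulsions are an expected event, the exclusion criteria remove patients with seizure disorders, and the Discussion gives concern about complications as a reason for the stimulation approach chosen.
- Patients enter within a month of infarction with a modified Rankin Scale (mRS) score of 2 to 4. They already have some disability, so a rule based on severe disability separates new serious events poorly from the existing condition.

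At stake is whether the gravest events reach the PI and the IRB promptly and carry the right label in the safety report.

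**Working it through.** No arithmetic applies, because the point rests on no rate, power or sample size. The check takes the definition as written and asks which stream each type of event would enter.

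**Inputs.** The definition, the two reporting rules and the list of expected events come from Incidence of adverse events. The hospital stay and follow-up come from Study design and Table 2.

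| Event | Within the definition as written? | Reporting that follows |
|---|---|---|
| Persistent or significant disability | Yes, if severe | Immediate, to PI and IRB |
| Death | Not named | To PI and IRB, no deadline |
| Life-threatening event with recovery | Not named | To PI and IRB, no deadline |
| Event requiring or prolonging hospitalisation | Not named | To PI and IRB, no deadline |
| Convulsion with full recovery | Not named; depends on what malfunction means | To PI and IRB, no deadline, unless it is read as a malfunction |

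The first four rows are the usual criteria. One is covered, and only in its severe form; three are not.

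The hospitalisation row has practical content here. Patients are inpatients for the 3-week intervention, so an event can prolong the stay. They are then discharged and seen again 4 weeks after the intervention ends, so an event can also lead to readmission. Neither case meets the definition unless it also causes severe disability or malfunction.

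**The second safeguard.** The monitoring committee consists of the PI and the two device coordinators, and its reporting line runs, when needed, to the PI. The PI is therefore both a member and the recipient. The only independence the section claims is from sponsors. The IRB is thus the one recipient of event reports outside the trial team that these two sections name, and the speed at which it hears depends on the definition above.

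**The case against.** **The events are not lost.** A reader might infer that nobody independent would ever see a death or a recovered seizure. The article contradicts that: all adverse events go to the IRB as well as to the PI. What is missing is the deadline and the serious label, and the point is limited to those.

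**The wording leaves room.** Malfunction is undefined and no duration is set, so a convulsion could be taken as a malfunction, and death as the extreme of disability. This is a fair reading and stands in part. But the article's own account of the mRS gives death a score apart from the disability grades, and a reporting rule should not depend on how each reader takes an undefined word.

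**The article condenses a fuller protocol.** Ministry and ethics approvals are cited, and the additional files are not shown. They may hold a complete list. That would excuse silence, but it does not excuse a definition written out in narrower terms.

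**The effect on the safety results cannot be sized.** A reader might infer that serious-event counts by arm would be too low to support a safety conclusion, or might quote a confidence limit for zero events among 15 patients. Neither measures this defect. The limit depends on 15 per arm and is the same under any definition. Convulsions are recorded in detail and can be tabulated by arm whatever their label.

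**Causality and the committee.** The article says that the CRC records causal relationship, not that the CRC alone judges it, so no finding is made there. Nor does it call the committee independent of the trial team. A wholly independent committee for a 60-patient, single-centre pilot is largely a design preference. What remains is the circular reporting line, a smaller drafting fault.

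**Conclusion.** The concern holds as a fault in a stated rule. Taken literally, the definition classes deaths, life-threatening events and events requiring or prolonging hospitalisation as non-serious. It does the same to convulsions with recovery unless they are read as malfunction. All of these then go to the PI and the IRB without a stated deadline. Three of the four usual seriousness criteria are missing, and so is a rule for an event that the article itself expects.

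This rests on two assumptions: that the definition is applied as printed, and that no fuller document in use at the site overrides it. If one does, the article still needs to agree with it.

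The committee point is secondary. The group has no member outside the trial team and reports to one of its own members, which the text should acknowledge and correct. The documents do not support a claim that events would go unseen, or any numerical estimate of bias in the safety results.

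**What to change.** **Incidence of adverse events.** Replace the definition with: a serious adverse event is any event that results in death, is life-threatening, requires or prolongs hospitalisation, or results in persistent or significant disability. Add that any convulsion is reported immediately to the PI and the IRB, whatever its outcome.

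**Data monitoring.** State that the committee is the PI and the device coordinators and has no member outside the trial team. Have it send its monitoring results to the IRB rather than only to the PI.

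**Cost.** One revision of the adverse event form, two changes of wording and slightly more expedited reports. The reporting route to the IRB already exists, so no new body is needed. The article describes the trial as ongoing, so events already on file should be reclassified under the new wording so that one definition applies to all patients.
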